**Figure 2 figure2:**
[figure not shown]
OpenViBE [29] implementation of the P300 speller. The next target letter in the word “dog,” “o,” is currently highlighted in blue. The previous letter, “d,” was correctly identified by the speller and is therefore highlighted in grey. The target symbols are displayed below the grid of letters and numbers (“Target:”), and the previously identified symbols can be seen below the target (“Result:”).

##### Calibration Phase

The calibration phase is used to collect training data for the spatial filter and classifier. The participants will complete 2 runs, where the words “the” and “quick” are copy-spelled without feedback. The recorded EEG signals from both runs are concatenated and then used to first train the xDAWN spatial filter before the linear discriminant analysis classifier is trained. Both target and nontarget trials are separated into epochs ranging from stimulus onset to 600 milliseconds poststimulus. The spatial filter is trained using the continuous EEG signals as well as the target epochs, whereas the classifier uses target and nontarget epochs for training.

##### Evaluation Phase

Once the spatial filter and classifier are trained, the participants will copy-spell the word “dog.” If at least 2 of the 3 letters are correctly identified by the P300 speller, the participant will move on to the training phase. Otherwise, the spatial filter and classifier will be retrained with the added EEG signals from the latest run. They will then copy-spell the word “fox.” If only 1 of the 3 letters is identified correctly, the participant will be removed from the study.

##### Training Phase

During the training phase, all participants will copy-spell the word “beautiful” for 5 runs. Ten flashes per row and column are used for the first run of the training phase, for all groups. The number of flashes in all subsequent runs is adapted randomly (control group 2) or based on the participants’ performance in the previous run (control group 1 and experimental group). The participants in all groups will receive feedback but will not be told why the number of flashes varies in each run.

The details of the task difficulty adaptation for each group are described below:

*Control group 1*: The adaptation algorithm in control group 1 is a replication of the work described in [17]. The number of flashes in each run, *N_i_*, is the average of the minimum number of flashes needed to reach more than 66% spelling accuracy in the previous run, referred to as *N*_(*i*–1)66_, and the actual number of flashes used in the previous run, *N*_*i*–1_, that is,

where *N_i_* is rounded to the nearest integer. If the spelling accuracy in the previous run was below 66%, then the number of flashes in the next run is increased by 1, that is,

*N_i_*=*N_i_*_–1_ + 1. **(5)**

*Control group 2*: The task difficulty adaptation of control group 2 is not based on the participants’ performance. Instead, the number of flashes in each run is chosen at random between 1 and 10 flashes. Choosing the number of flashes in this way will expose the participants in control group 2 to varying task difficulties in an unpredictable way. This allows the authors to compare the personalized adaptation approaches of the other 2 groups to a nonadaptive difficulty adjustment approach under similar conditions. Using a constant task difficulty in this group would potentially lead to differences due to an easier average task difficulty [36] and reducing the number of flashes by the same amount each run would introduce predictability, which the other groups do not have.

*Experimental group*: In the experimental group, a P-type ILC controller is used to adapt the number of flashes in the next run, *N_i_*, based on the number of flashes and error in the previous run, *N_i_*_–1_ and *e_i_*_–1_=1-*J*_1(
*i*–1)_ (where *J*_1_ is the spelling accuracy). The update law of the controller is

*N_i_*=*N_i_*_–1_+ϵ*f*(*e_i_*_–1_), **(6)**

where ε is a controller parameter and

*f*(*e*_i–1_)=2*e_i_*_–1_–1. **(7)**

Figure 3 shows *f*(*e_i_*_–1_) against *e_i_*_–1_. As can be seen, if only half of all symbols in the previous run were identified correctly, that is, 50% error, *f*(*e_i_*_–1_) will be 0, which means that the number of flashes in the next run will remain the same as that in the previous run. *f*(*e_i_*_–1_) will be –1, if all symbols were identified correctly, and1 if no symbols were identified correctly. This means that the controller parameter *ϵ* is the maximum update step of the number of flashes from one run to the next. ε was tuned in simulation and pilot experiments to the following:

The update law described in (6), (7), and (8) can therefore be simplified to

*N_i_*=*N_i_*_–1_(*e_i_*_–1_+0.5). **(9)**

The new number of flashes, *N_i_*, is then rounded up to the next highest integer.

**Figure 3 figure3:**
[figure not shown]
The function of the error in the previous run, f(e_i–1_), used in the P-type ILC update law, plotted against the error in the previous run, e_i–1_.

##### Posttraining Phase

After the training phase, which differs for each group and individual, the participants in all groups will copy-spell the word “dance” with 12 flashes per row and column. This is done to compare any posttraining differences between the groups.

### Data Analysis

The offline data analysis steps closely follow the steps described by Arvaneh et al [17] to allow for comparability of results.

#### Questionnaire

The answers to Arvaneh et al’s [17] questionnaire will be analyzed for between-group and within-group differences, using statistical tests, such as repeated measures ANOVA and paired *t* tests.

Similarly, between-group differences in responses to the NASA Task Load Index questionnaire [32] will be analyzed, for example, using a 1-way ANOVA. The raw score of each question will be used for the data analysis.

#### RDM Task

The change in performance in the RDM task between pre- and posttraining phases will be analyzed in terms of accuracy and response time. The accuracy is the number of correct trials over the total number of trials, and the response time is the elapsed time between onset of the coherent motion until the correct button is pressed before the end of the coherent motion. The response time of incorrect trials will not be considered. The mean response time will be calculated for each participant individually. Statistical tests, such as ANOVA and paired *t* tests, will be conducted to analyze between-group and within-group differences for both the accuracies and mean response times.

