### Participants

The participants will be healthy individuals aged 18 years or older with no self-reported history of neurological or cognitive illness, and normal or corrected-to-normal vision. Interested participants who do not meet these criteria, have a negative reaction to the electroconductive gel, or who are illiterate will be excluded from the study.

Based on previous work using a P300-based BCI for attention training [17,26], a sample size of 45 participants (15 per group) was determined. Participant recruitment will continue until the sample size is reached. It is expected that around 50 participants will be recruited due to a 10% dropout rate.

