### Procedure

The experimental procedure of this study is based on previous work by Arvaneh et al [17]. An overview of the procedure can be found in Figure 1.

Participants will be asked to fill in a questionnaire at the beginning and end of the experiment. They will then complete a continuous random dot motion (RDM) task, which will serve as a baseline for their cognitive abilities. Afterward, participants will receive attention training using a P300 speller task, where the task difficulty in each run of the speller is either chosen randomly (control group 2) or adjusted to the participant’s performance (control group 1 and experimental group). To analyze improvements in cognitive abilities, participants are asked to complete the RDM task again after the training.

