##### ERP Components

The changes in the ERP components throughout the training will be analyzed. For this purpose, epochs from 150 milliseconds to 550 milliseconds poststimulus onset will be extracted from the EEG data for both target and nontarget trials. Subsequently, the total power across the same centroparietal electrodes as used in [17] (ie, C3, Cz, C4, P3, Pz, and P4) will be calculated for each epoch.

The average total power for all epochs of the calibration and evaluation phases, the training phase, and the after-training phase, respectively, will be calculated. A training-to-calibration ratio of the average power for both target and nontarget trials will be obtained by dividing the average total power during the training phase by the average total power during the calibration and evaluation phases. The same will be done with the average total power during the after-training phase to obtain an after-training-to-calibration ratio.

A ratio of greater than unity indicates an increase in average total power, whereas a ratio of less than unity indicates a decrease in average total power compared to the calibration and evaluation phase. For target trials, an increase in power means that the participant improved their attention, and a decrease in power of nontarget trials can be interpreted as the participant being less distracted by nontarget flashes [17].

Appropriate statistical tests, such as ANOVA, will be conducted to analyze within-group and between-group differences in the aforementioned ratios.

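### Measured baselines enter the arm comparisons only as change scores or raw ratios, and the EEG ratios are read against 1, which their null mean exceeds

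*Protocol article*

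**What the plan says.** The Procedure section treats the pre-training RDM task as a baseline: "They will then complete a continuous random dot motion (RDM) task, which will serve as a baseline for their cognitive abilities". The four Likert items are also answered before and after training, and calibration and evaluation EEG power is computed for every participant.

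The Data Analysis sections use these values as follows.

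- **RDM Task:** "The change in performance in the RDM task between pre- and posttraining phases will be analyzed in terms of accuracy and response time", and then "Statistical tests, such as ANOVA and paired *t* tests, will be conducted to analyze between-group and within-group differences".
- **Questionnaire:** responses "will be analyzed for between-group and within-group differences", with repeated measures ANOVA and paired *t* tests as examples.
- **ERP Components:** average total power in the training and after-training phases is divided by calibration and evaluation power. A ratio above 1 is taken as an increase, which for target trials means better attention. A fall for nontarget trials means less distraction. "Appropriate statistical tests, such as ANOVA, will be conducted to analyze within-group and between-group differences in the aforementioned ratios".
- **Time-Frequency Analysis:** the same ratios are formed for alpha power. Values below 1 are read as less distraction, and only between-group tests are named.

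No section names a baseline covariate or a log scale. On size, "a sample size of 45 participants (15 per group) was determined"; no effect size, SD, power or alpha is given.

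**The concern.** There are two separate issues.

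**Precision.** With two time points, the group-by-time interaction in a repeated measures ANOVA is the same test as a comparison of change scores. Either reading of the RDM plan therefore leads to the change-score contrast. That contrast fixes the slope on baseline at 1, whereas ANCOVA estimates it. With 15 per arm the difference can be material. The Objectives expect cognitive gains to be similar across arms, and how much support that expectation can get depends on how tightly the RDM and EEG contrasts are estimated.

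**The reference value of 1.** The protocol itself fixes unity as the no-change point for the EEG ratios. A ratio of two noisy positive quantities is right-skewed, so its arithmetic mean lies above 1 when the two phases do not differ. For target trials this leans towards the hoped-for finding of improved attention. For nontarget and alpha power it leans against the hoped-for decrease. The Results section expects improvement in every group, so within-group readings will matter.

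**Working it through.** **Inputs from the protocol.** Three arms, 15 per arm, 45 in total; 10% dropout; about 50 to be recruited. Check: 45 / (1 − 0.10) = 50, which reproduces. The 45 itself cannot be reproduced, because its statistical inputs are not stated.

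**Assumptions (not in the protocol).** Two-sided alpha 0.05; a true difference of 0.8 SD for one pairwise contrast; equal pre and post SD (set to 1); pre-post correlation r from 0.3 to 0.9; log-ratio SD s from 0.2 to 0.4.

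**Step 1: variance of the arm contrast.** Per-participant variance is

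- post value only: 1
- change score: 2(1 − r)
- ANCOVA: 1 − r²

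The ratio of ANCOVA to change score is (1 − r²) / [2(1 − r)] = (1 + r)/2, that is 0.65, 0.75, 0.85 and 0.95 at r = 0.3, 0.5, 0.7 and 0.9. Estimating the slope costs one error degree of freedom and multiplies the ANCOVA variance by 41/40.

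**Step 2: power.** The noncentrality is (0.8/σ)·√(15/2), with 42 error df for the change score and 41 for ANCOVA. At r = 0.5:

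- change score: σ² = 1.00, noncentrality 0.8 × 2.739 = 2.19, power 57%
- ANCOVA: σ² = 0.75 × 41/40 = 0.769, noncentrality 2.50, power 68%

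| r | Post value only | Change score | ANCOVA |
|---|---|---|---|
| 0.3 | 57% | 44% | 60% |
| 0.5 | 57% | 57% | 68% |
| 0.7 | 57% | 79% | 84% |
| 0.9 | 57% | 99.8% | 99.8% |

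Simulation agrees: 57% v 69% at r = 0.5 and 79% v 84% at r = 0.7. Below r = 0.5 the change score does worse than ignoring the baseline. The smallest difference detectable with 80% power, change score v ANCOVA, is 1.24 v 1.01 SD at r = 0.3, 1.05 v 0.92 at 0.5, 0.81 v 0.76 at 0.7 and 0.47 v 0.46 at 0.9.

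For EEG power, a log ratio is a change score on the log scale. The same formulas therefore apply there, with r the correlation of the log powers, and approximately to raw ratios of modest spread.

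**Step 3: raw ratio when nothing changed.** If the log ratio is normal with mean 0 and SD s, the mean ratio is exp(s²/2):

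- s = 0.2: exp(0.020) = 1.02
- s = 0.3: exp(0.045) = 1.05
- s = 0.4: exp(0.080) = 1.08

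A one-sample *t* test of the raw ratios against 1 in an arm of 15 falsely finds a mean above 1 in 3.6%, 4.5% and 5.3% of simulated trials respectively, against a nominal 2.5%. On the log scale the null mean is exactly 0 and the excess disappears.

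**Step 4: between arms.** Under no arm effect the upward shift is the same in each randomised arm. Simulated one-way ANOVA on the raw ratios rejects 4.4% to 5.0% of the time at the 5% level, so the arm comparison is not biased.

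**The case against.** The strongest objection is that the protocol leaves its tests open. The analysis sections introduce their tests with the phrase such as, so ANCOVA is not excluded, and an analysis plan that is not shown could specify it. Change-score and repeated measures analyses are valid under randomisation, so the preference for ANCOVA is about efficiency. The protocol also gives a reason for its choices: comparability with the study it replicates. All of this stands, and it limits how strongly the point can be put. It does not remove it. The RDM section already names change as the quantity analysed, and the two EEG sections already define raw ratios and unity as the reference. Comparability is kept if the replicated analyses are reported alongside.

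A reader might infer three stronger things that the document does not support.

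- **That arms will be compared by which paired test is significant.** If all arms shared one standardised effect of 0.5, power per arm would be 0.438, and the three tests would disagree 1 − 0.438³ − 0.562³ = 74% of the time. But the protocol lists paired tests beside ANOVA for within-group and between-group questions together. It nowhere says that paired tests replace the between-arm test.
- **That the ratio bias distorts the arm comparison.** Step 4 shows that under the null it does not.
- **That the false above-1 rate is far from nominal.** Pooling all 45 participants gives 7.8% to 18.5% over the same range of s, but the protocol states no pooled test against 1.

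It is also fair to note that the main expected arm difference is training length, which has no baseline value and is untouched by this point.

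**Conclusion.** The point holds as two limited statements.

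First, the methods named for the RDM, questionnaire and EEG arm comparisons give up precision that the collected baselines could supply. The loss at 15 per arm is 16 percentage points of power at r = 0.3, 11 at r = 0.5, 5 at r = 0.7 and none at r = 0.9, for an assumed 0.8 SD difference. The protocol states neither r nor an effect size, so the actual loss is unknown within that range. The one qualification is that for r above about 0.95 the cost of the slope, (1 + r)/2 × 41/40, takes the variance ratio just past 1; the effect is negligible.

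Second, reading the mean of raw EEG ratios against 1 has a modest built-in upward lean: a null mean of 1.02 to 1.08 and a one-sided error of 3.6% to 5.3% in an arm of 15 for an assumed log-ratio SD of 0.2 to 0.4. It concerns within-group readings only.

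Neither makes the planned comparisons invalid. Both are worth correcting because the correction needs no new data.

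**What to change.** - **RDM accuracy, RDM response time and each Likert item:** estimate between-arm effects by ANCOVA of the post-training value on arm plus the pre-training value.
- **Total power and alpha power:** model log power in the training or after-training phase on arm plus log calibration-and-evaluation power, and report geometric mean ratios. Make any within-group reading against 1 on the log scale.
- **Paired tests and raw ratios:** keep them as secondary results for comparability with the replicated study, and state that arm comparisons rest on the ANCOVA contrasts.
- **Training length:** no change.

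The cost is a few sentences of analysis text and one covariate per model. Data collection, procedures and sample size stay as they are.

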#### P300 Speller Task

##### Spelling Accuracy

The between-group differences in performance in the P300 speller in terms of spelling accuracy will be analyzed for all participants. Only the evaluation run, the first run of the training phase, and the posttraining run will be considered, as these 3 runs use the same number of flashes per row and column for all participants. Training runs 2-5 are different for each individual as the number of flashes is either determined by their previous performance (control group 1 and experimental group) or chosen randomly (control group 2). This means that the performance during these runs cannot be compared directly.

##### Length of Training

Since 1 of the objectives of this study is to accelerate attention training, the length of the training will be compared in terms of the total number of flashes used in runs 2-5 of the training phase. A statistical test, such as the 1-way ANOVA, will be carried out to compare between-group differences.

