### Objectives

The primary objective of this study is to accelerate P300-based attention training by progressively and optimally adjusting the task difficulty in a training session to each individual using ILC. The proposed iterative learning controller, which determines the task difficulty based on previous performance and task difficulty level, will be compared to the adaptation algorithm used in a previous study by Arvaneh et al [17]. Thus, we will be able to analyze the replicability of Arvaneh et al’s [17] study. A random task difficulty control group will also be used in this study to compare the training effects of personalized approaches with the training effects due to exposure to a range of nonpersonalized task difficulty levels.

While we expect the cognitive enhancements achieved during the training session to be similar among the groups, we expect the experimental group, where the task difficulty is determined by an iterative learning controller, to complete the training session more quickly than the other groups.

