#### P300 Speller Task

##### Overview

In this study, the P300 speller implementation in OpenViBE [29] is used. This P300 speller uses the xDAWN algorithm [35] to train a spatial filter that enhances the SNR of the P300 ERPs. This reduces the 32 EEG channels to 3 components, which are weighted combinations of all channels. A linear discriminant analysis classifier is used to distinguish target and nontarget trials. It should be noted that the row and column with the highest probability of belonging to the target class are chosen, even if that is below 50%. Both the spatial filter and classifier are trained for each participant using calibration data.

Figure 2 shows the 6 by 6 grid of letters and numbers that is displayed on the screen. The word to be copy-spelled and the identified symbols can be seen below the grid. If the identified symbol is the same as the target symbol, it will be displayed in green. If the identified symbol is in the same row or column as the target symbol, it will be displayed in orange and if it is wrong, it will be displayed in red.

Outside of the training phase, 12 flashes per row and column are used. Each flash lasts 55 milliseconds with an interflash interval of 117 milliseconds. Each target symbol is highlighted in blue for 6 seconds before the flashing begins.

In each run after the calibration phase, the spelling accuracy, that is, the fraction of symbols that were identified correctly, is calculated for all numbers of flashes between 1 and the actual number of flashes used.

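### The named test for training length leaves out training run 1, a covariate shared by all arms that can sharpen the comparison of ILC with control group 1

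*Protocol article*

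**What the plan says.** Under Objectives, the article states: "The primary objective of this study is to accelerate P300-based attention training". The ILC controller "will be compared to the adaptation algorithm used in a previous study", and the experimental group is expected "to complete the training session more quickly than the other groups".

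Under Data Analysis, Length of Training, "the length of the training will be compared in terms of the total number of flashes used in runs 2-5 of the training phase". The analysis is then given as: "A statistical test, such as the 1-way ANOVA, will be carried out to compare between-group differences". This section names no covariate.

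On run 1, Training Phase says: "Ten flashes per row and column are used for the first run of the training phase, for all groups". The P300 Speller Task overview says that, in each run after calibration, spelling accuracy "is calculated for all numbers of flashes between 1 and the actual number of flashes used". Accuracy at each of 1 to 10 flashes is therefore available for run 1 in all three arms. The Spelling Accuracy section uses run 1 only as an outcome in its own right.

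**The concern.** In the ILC arm and control group 1, training length depends on how well a participant's P300 is decoded, as well as on the adaptation rule. Someone who is decoded well is moved quickly to few flashes under either rule; someone who is decoded badly stays at many. Run 1 measures this under the same conditions in every arm, before the rules take effect. A 1-way ANOVA puts all of this variation between people into the error term.

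What is at stake is precision. With 15 per arm, a wide spread in decoder quality can hide a real saving in flashes, although the data needed to account for much of that spread are already collected.

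**Working it through.** **The plan's own figures.** The article gives 45 participants (15 per group) and about 50 recruited with 10% dropout: 45 / 0.9 = 50, which agrees. It states no alpha, power, effect size or SD for training length, so the size of this point cannot be computed from the article alone. Two-sided 0.05 is assumed below. Flashes are counted per row and column and summed over runs.

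**1. The link from run 1 to run 2 is arithmetic.** The training word has nine letters and run 1 uses 10 flashes.
- ILC: N2 = 10 × (e + 0.5), rounded up. With 9/9 correct, 10 × 0.5 = 5. With 8/9, 6.11 becomes 7. With 7/9, 7.22 becomes 8. With 6/9, 8.33 becomes 9. With 5/9, 9.44 becomes 10.
- Control group 1: N2 is the average of 10 and the smallest flash count that exceeded 66% accuracy in run 1, rounded to the nearest integer, or 10 + 1 = 11 if accuracy was below 66%.

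So in both adaptive arms one of the four summands of the outcome is fixed by run 1, and run 3 builds on it.

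**2. Control group 2 is different.** Its counts are drawn at random from 1 to 10. If the draws are uniform, the variance of the sum over four runs is 4 × (10² − 1)/12 = 33 (SD 5.74). None of it comes from decoding and no covariate can remove it.

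**3. Gain for any assumed correlation.** Adjustment multiplies residual variance by (1 − ρ²). For an assumed difference of 0.8 SD and n = 15 per arm, the noncentrality is 0.8/√(1 − ρ²) × √(15/2).

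| ρ | noncentrality | power |
|---|---|---|
| 0 | 2.19 | 0.56 |
| 0.3 | 2.30 | 0.60 |
| 0.5 | 2.53 | 0.68 |
| 0.7 | 3.07 | 0.84 |

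**4. Plausible size of ρ, by simulating the stated rules.** The covariate is run 1 mean accuracy over 1-10 flashes, with a common slope.

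*Model A:* letter accuracy at n flashes = 1/36 + (35/36)(1 − exp(−(n/k)^1.5)), with k lognormal between people and median 2-5.

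| Log-SD of k | Variance removed, ILC vs control 1 | Power, unadjusted to adjusted | Variance removed, three arms, common slope |
|---|---|---|---|
| 0.1-0.2 | about 15-46% | 0.99-1.00 to 1.00 | about 1-15% |
| 0.4-0.6 | 66-82% | 0.65-0.67 to 0.99 (poor or very variable decoders); 0.86 to 1.00 (middle); 0.96-0.99 to 1.00 (good) | about 13-44% |

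*Model B:* Gaussian score per flash, lognormal decoder strength, the evaluation-phase exclusion applied, and optional run-to-run drift.

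| Median strength | Log-SD | Drift | Variance removed, ILC vs control 1 | Power, unadjusted to adjusted |
|---|---|---|---|---|
| 0.9 | 0.05 | 0 | 26% | 0.94 to 0.99 |
| 1.1 | 0.1 | 0 | 38% | 0.96 to 1.00 |
| 1.1 | 0.15 | 0.3 | 46% | 0.66 to 0.88 |
| 1.1 | 0.3 | 0.3 | 59% | 0.32 to 0.64 |
| 1.1 | 0.3 | 0 | 76% | 0.39 to 0.92 |
| 1.5 | 0.4 | 0 | 81% | 0.49 to 0.98 |

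In Model B the covariate explained 0% of the variance in control group 2. A common slope across three arms removed about 1-50%.

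**5. Slopes differ between the adaptive arms.** Under Model A with median k = 2 and log-SD 0.4, the slopes are about −18 (ILC) and −30 (control group 1) flashes per unit of accuracy. Fitting a separate slope in each of these two arms left power under Model A unchanged.

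**The case against.** The strongest case against runs as follows.

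- **The wording leaves ANCOVA open.** The ANOVA is given as an example in a condensed article, and a fuller analysis plan may name a covariate. That is fair, and the article contains no contradiction. But the one method it names for the outcome behind its primary objective is unadjusted, and a covariate chosen after the data are seen would be open to challenge.
- **The gain may be negligible.** The participants are healthy, probably young, and those who spell badly in the evaluation phase are removed, so decoder spread may be narrow. The two rules also differ almost by construction. For a participant spelled correctly at every flash count, ILC gives 5 + 3 + 2 + 1 = 11 and control group 1 gives 6 + 4 + 3 + 2 = 15. This stands: with narrow spread, adjustment changes almost nothing.
- **Attention may shift during training, so run 1 predicts less.** This also stands in part. Drift lowers the gain but did not remove it in the scenarios run.
- **The model is not as simple as one extra term.** Correct, because the slopes differ by arm.

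A reader might go further and infer that most of the error variance of the named three-arm ANOVA is avoidable. The documents do not support that. Control group 2's counts are random by design, a common slope removes at most about half under the models tried, and the article reports no variance to split. Nor does chance imbalance in decoder quality bias the unadjusted test: under randomisation it is ordinary sampling error, already reflected in the standard error.

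**Conclusion.** The point holds as one of efficiency, confined to ILC against control group 1. Run 1 is a valid covariate: it is common to all arms, precedes their divergence and is already collected. In both adaptive arms it determines part of the outcome.

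Adjustment removes from about 15% of residual variance, with little to gain in power, to about 80%, with a large gain. Which end applies depends on the spread of decoder quality between people, which the article does not give. All variance shares and power values therefore rest on the assumed accuracy models, uniform draws in control group 2 and a two-sided 0.05 test. Adjustment did not lower power in any scenario run. The figures do not show that the trial is underpowered.

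**What to change.** In Length of Training, pre-specify an ANCOVA of total flashes in runs 2-5 for the ILC arm against control group 1. The covariate is run 1 mean spelling accuracy over flash counts 1 to 10, centred at its overall mean, with arm-specific slopes allowed because the two rules respond differently to performance. The arm coefficient is then the difference in flashes at average run 1 performance. Report it with its 95% CI and keep the unadjusted comparison as a sensitivity analysis. If control group 2 stays in the same model, give it its own slope.

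The cost is a sentence or two of text and one degree of freedom for a common slope, two for separate slopes in the adaptive arms, or three with control group 2 included. No new data, participants or procedures are needed.
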